#### Model checking

The logistic regression model for the primary analysis is prespecified. However, observations identified as potential outliers through their influence on the model, may be excluded as part of a sensitivity analysis. The distributional assumptions of multivariable linear regression models will be visually assessed through plots of residuals. If there are concerns about distributional assumptions being met, bootstrapped CIs for the adjusted between-group differences will be produced.

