### Determination of sample size

Since the planned primary analysis is a comparison of the proportions of the binary primary outcome, the sample size calculation was based on a two-sided Fisher exact test. An abstinence rate of 5% for the control group and detectable effect of 6% (ie, an increase from 5% to 11% due to the intervention) are conservative estimates consistent with those from the EARS pilot study^15^ and those reported from a systematic review of pharmacological interventions.^38^ The corresponding OR for this effect size is 2.35. Participants with missing outcome data will be assumed to be still smoking following the Russell Standard,^39^ and the numbers of participants in each allocated group are assumed to be in the ratio of 1:1. Under these conditions, according to Stata V.14.2, the minimum number of participants required to detect an abstinence rate of 11% compared with that of 5% in the control group, with a significance level of no more than 5% and power of at least 90%, is 900, above which a power in excess of 90% is maintained.

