### Primary analysis

The null hypothesis is that there is no difference in CO verified 6-month prolonged floating abstinence rates between the intervention and control groups at 9 months post-baseline. In line with the Russell Standard schedule,^39^ the primary comparative analysis will be conducted on an ITT basis, in which participants with missing responses will be considered to still be smokers. Interpretation of the primary effectiveness analysis will be based on the OR from the logistic regression model adjusted for (fixed effect) stratification variables: site as a factor and HSI as an ordinal covariate. Both the adjusted (primary analysis) and unadjusted ORs and corresponding 95% CIs will be presented. Primary effectiveness shall also be presented as a relative risk along with the absolute between-group differences in abstinence rates, as recommended in the CONSORT guidelines for parallel group randomised trials.^58^

Planned sensitivity analysis of the primary outcome:

Rather than assuming participants with missing responses at 3 or 9 months were still smoking, the primary outcome will be imputed under a number of varying assumptions and the primary analysis re-run for each of the scenarios.A complier average causal effect analysis will be undertaken, if greater than 20% of participants allocated to the intervention group are categorised as not having completed at least two intervention sessions with a health trainer, with individual participants in the intervention group categorised as compliers if they completed at least two intervention sessions. Participants in the control group and non-compliers in the intervention group will be compared with compliers in the intervention group.

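### Excluding participants for their influence on the primary logistic model removes almost only quitters, so that sensitivity analysis cannot check the primary result

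*Protocol article*

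**What the plan says.** Under Model checking, the protocol article fixes the logistic model for the primary analysis in advance and then allows that "observations identified as potential outliers through their influence on the model, may be excluded as part of a sensitivity analysis". It names no diagnostic or cut-off.

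The model and outcome are described under Primary analysis. CO-verified prolonged abstinence (yes/no) is regressed on arm, site as a factor and HSI as an ordinal covariate, by intention to treat, and "participants with missing responses will be considered to still be smokers". The planning rates are under Determination of sample size: "an increase from 5% to 11% due to the intervention". There, "The corresponding OR for this effect size is 2.35", and the total "with a significance level of no more than 5% and power of at least 90%, is 900".

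**The concern.** Deleting influential points makes sense when an extreme measured value may be distorting a fit. A verified yes/no outcome has no extreme values. When the event is uncommon and the covariates are few and bounded, the observations that fit worst and pull hardest on the coefficients are simply those with the event. They pull hardest in the arm where the event is rarer. An exclusion rule based on influence then drops randomised participants because they quit, and does so unequally by arm.

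A sensitivity analysis is read as support for the primary result or as a challenge to it. If the intervention works, this one would tend to return a larger OR than the primary analysis and could be taken as reassurance. It also sits badly with the intention-to-treat basis of the primary analysis.

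**Working it through.** **Inputs from the protocol article.** Control rate 5%, intervention rate 11%, total 900, "the numbers of participants in each allocated group are assumed to be in the ratio of 1:1" (so 450 per arm), and a two-sided Fisher exact test. Expected quitters: 0.05 × 450 = 22.5 control and 0.11 × 450 = 49.5 intervention, 72 in all, or 8% of 900.

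**The plan's own figures.** OR = (0.11/0.89)/(0.05/0.95) = 2.348, which agrees with 2.35. Exact enumeration of Fisher power gives 0.8996 at 898, 0.9003 at 900 and 0.9010 at 902, so 900 is reproduced.

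**Closed form, arm only.** The Pearson residual is r = (y − p)/√[p(1 − p)]. Leverage is h = 1/450 for everyone. With k = 2 coefficients, Cook's distance is D = r²h/[k(1 − h)²], which is close to r²/900.

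| Participant | r | r² | D (approx.) |
|---|---|---|---|
| Control quitter | √(0.95/0.05) = 4.36 | 19.0 | 0.0211 |
| Intervention quitter | √(0.89/0.11) = 2.84 | 8.09 | 0.0090 |
| Intervention non-quitter | −√(0.11/0.89) = −0.35 | 0.124 | 0.00014 |
| Control non-quitter | −√(0.05/0.95) = −0.23 | 0.053 | 0.00006 |

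The cut-off 4/n is 4/900 = 0.0044. Every quitter lies above it and every non-quitter far below. Within an arm, a quitter's D exceeds a non-quitter's by a factor of 19² = 361 (control) or (0.89/0.11)² = 65 (intervention).

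**With site and HSI in the model.** The article gives no HSI distribution and no HSI or site effects, so these were assumed and varied: HSI coded 0-6 or low/high, with and without HSI and site effects. Four scenarios of 500 trials each were run (900 participants, four sites, 5% versus 11%).

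| Rule | Who is flagged | Share of all quitters removed |
|---|---|---|
| Cook's D > 4/n | 99.3-100% quitters | 98.8-100%; model not estimable in any run |
| \|standardised Pearson residual\| > 2 | quitters only | 81-99.5% |
| \|standardised Pearson residual\| > 3 | quitters only | 43-52% |
| \|DFBETA\| for arm > 2/√n | 99.9-100% quitters | 84-86% |
| Cook's D > 1 | nobody (largest D seen 0.094) | 0% |

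The 20 largest Cook's distances belonged to quitters in all 2,000 trials. In separate runs the residual cut-off of 3 took 95-99% of control quitters but only about a third of intervention quitters.

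**Effect on the OR.** Dropping the 10 most influential participants removed 10 quitters, about 7 of them controls. Applied to the expected counts, that leaves 15.5 quitters and 427.5 non-quitters in control, and 46.5 and 400.5 in intervention:

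OR = (46.5 × 427.5)/(15.5 × 400.5) = 3.20.

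The simulations agree. The median OR went from about 2.4 to about 3.2-3.4 across separate sets of runs. Averaged on the log scale over the four scenarios, it went from about 2.4 to 2.6-2.9 after dropping 5 and to 3.1-3.6 after dropping 10.

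**The case against.** A reader might infer that the plan contains a rule that deletes the events. It does not. No diagnostic, cut-off or number to drop is stated; 4/n and the top 10 are illustrations chosen for this check. The article only summarises the main analyses, and a separate analysis plan may well name the diagnostic, so its absence here is not a fault. Nor must the step either remove every event or inflate the OR. At Cook's D > 1 nobody is removed, and at a residual cut-off of 3 about half the events remain.

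Influence can also be assessed per covariate pattern. Two arms, four sites and seven HSI values give 2 × 4 × 7 = 56 patterns, and removing a pattern takes out quitters and non-quitters together. In 300 simulated trials with an assumed HSI distribution, a pattern-level delta-beta above 1 flagged 0.7 patterns on average, and removing those moved the median OR from 2.37 to 2.33. Removing the single most influential pattern (about 26 people, about 4 of them quitters) gave 2.35; removing the top two or three gave 2.41 and 2.52. The inflation is therefore a property of participant-level deletion and not of all influence diagnostics.

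Finally, the step is optional, is not among the planned sensitivity analyses listed under Primary analysis, and leaves the primary estimate alone.

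All of this stands and limits the size of the point. The core remains. The article speaks of observations, most naturally individual participants, and on that reading a cut-off either flags almost only quitters or flags nobody. Naming a threshold in the analysis plan would not change that.

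**Conclusion.** The concern holds as a minor one, confined to the sensitivity analysis. Under participant-level diagnostics, the exclusion that the article permits is selection on the outcome. At the planning rates it ranges from no deletion (and no test), through an OR raised from about 2.4 to about 3.2-3.4 by dropping 10 people, to a model that cannot be fitted.

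The upward shift assumes that the planned effect is real. With no true effect the median OR stayed near 1, so the documents do not support a claim that the step would create an effect. The size of the shift depends on the observed rates and on the cut-off. The finding that those flagged are almost all quitters did not depend on the assumed HSI coding, HSI effect or site effect. The prespecified primary OR and its interpretation are unaffected.

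**What to change.** Replace the exclusion under Model checking, and any matching text in the analysis plan, with wording to this effect: influence diagnostics for the primary model will be reported descriptively; no participant will be excluded because of influence or residual size; exclusion or correction will be limited to verified data errors identified blind to arm.

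A penalised (Firth) logistic model with the same covariates could be added as a robustness check but is not required. About 72 expected events for six coefficients (intercept, arm, three for site, one for HSI) does not by itself show a need for it.

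The cost is a change of wording, with no new data and no required extra model. The article says that the analysis plan is to be approved before database lock, so the change can be made there.

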### Mediational analysis

If there is evidence that the intervention is effective, an exploratory mediational analysis will be undertaken to determine if any effect of allocated group on the primary outcome was mediated by changes in smoking and/or physical activity between baseline and 3-month follow-up, adjusted for the stratification variables (site and HSI). Further analyses will explore if changes in smoking and physical activity are mediated by changes in outcomes from the questionnaire on attitudes to smoking between baseline and 3 months (importance and confidence to reduce smoking/increase physical activity; self-monitoring and goal setting; urges to smoke).

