#### Primary outcome measure

Biochemically verified 6-month floating prolonged abstinence between 3 and 9 months.^40^ Abstinence will be confirmed by expired CO <10 ppm measured with a CareFusion MicroCO metre (Williams Medical Supplies, Rhymney, UK, www.carefusion.co.uk) at a face-to-face visit.

Participants who self-reported abstinence at 3 months and who were confirmed as abstinent through biochemical verification via expired CO at a face-to-face assessment and then self-report abstinence (and not having smoked even a puff since the 3-month assessment) at 9 months, again confirmed by expired CO, will be defined as having prolonged abstinence over at least 6 months.

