#### Other smoking-related measures

Only participants who have biochemically verified abstinence at 9 months are being contacted at 15 months post-baseline to assess floating prolonged abstinence over a period of 12 months (3–15 months). Participants who were not abstinent at 3 months but have biochemically confirmed abstinence at 9 months will be contacted at 15 months to confirm floating prolonged abstinence of 6 months between 9 and 15 months. As a contingency measure for verification of abstinence during the COVID-19 outbreak, abstinence will be confirmed by saliva cotinine level <12 ng/mL^41^ using a mailed self-collection kit and assay provided by ABS Laboratories (York, UK, www.acmgloballab.com). This contingency measure will apply to follow-up for secondary outcomes for a minority of participants. While the intervention is expected to primarily influence quitting in the first 3 months of the study, it is possible that a sustained quit attempt occurs after the 3-month assessment as a result of the health trainer building behaviour change skills which are used subsequently to reduce and then quit smoking.

Participants are asked to self-report the number of cigarettes smoked and type of nicotine product (ie, pipes, cigars and roll your own). We estimated 0.45 g of tobacco was the equivalent of one cigarette based on a previous rigorous study^42^ and reported in the EARS pilot study.^15^ From this we will estimate the number of cigarettes smoked at follow-up, and also calculate if participants reduce smoking by at least 50% between (1) baseline and 3 months, and (2) baseline and 9 months.

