#### Analysis of secondary outcomes

Between-group comparisons will be undertaken, including for the following key secondary outcomes:

Biochemically verified point prevalence abstinence at 3, 9 and 15* months post-baseline.Self-reported point prevalence abstinence at 3, 9 and 15* months post-baseline.Prolonged biochemically verified abstinence over 6 months between 9 and 15 months post-baseline.Prolonged biochemically verified abstinence for at least 12 months between 3 and 15 months post-baseline (derived from biochemically confirmed abstinence at all three follow-up time points).At least a 50% reduction in reported smoking levels between (1) baseline and 3 months, and (2) baseline and 9 months.Number of cigarettes used on an average day over the past week (including equivalent cigars, tobacco) at 3, 9 and 15* months post-baseline.Total number of LNCP used on an average day over the past week at 3, 9 and 15* months post-baseline.Total number of self-reported minutes engaged in MVPA over the past week at 3 and 9 months post-baseline.BMI at 3 and 9 months post-baseline.

NB: * only for those with biochemically confirmed abstinence at 9 months.

The following data are derived from accelerometers mailed to a subgroup of participants in both arms of the trial along with the 3-month questionnaire, which are returned after the accelerometers have been worn for 7 days:

The average time spent in moderate to vigorous activity over the past week.The average daily time spent sleeping over the past week.

No adjustment for multiple analyses will be made; such adjustment methods are too conservative when outcomes are positively correlated, as they would be in this trial. Analyses will use multivariable linear regression (continuous outcomes) or logistic regression (binary outcomes) to compare each of these secondary outcomes between allocated groups, with adjustment for site as a factor, and HSI, as an ordinal variable, as well as baseline values of the outcome as appropriate. As accelerometer data were only available at 3 months, only summary statistics for weekly minutes of MVPA shall be presented by allocated group without adjustment for baseline variables.

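### Change in smoking to 3 months is tested as a mediator of an outcome that already requires abstinence at 3 months, so the result cannot show that cutting down led to quitting

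*Protocol article*

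**What the plan says.** The protocol article (Mediational analysis) states: "If there is evidence that the intervention is effective, an exploratory mediational analysis will be undertaken". Its purpose is to find out "if any effect of allocated group on the primary outcome was mediated by changes in smoking and/or physical activity between baseline and 3-month follow-up". Site and HSI enter as covariates. The mediators and the outcome are therefore named in the article itself.

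The outcome is defined under Primary outcome measure as "Biochemically verified 6-month floating prolonged abstinence between 3 and 9 months". It has two parts:

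- **Month 3.** It is open to "Participants who self-reported abstinence at 3 months and who were confirmed as abstinent through biochemical verification via expired CO at a face-to-face assessment".
- **Months 3 to 9.** They must then report abstinence at 9 months, "and not having smoked even a puff since the 3-month assessment", again with CO confirmation.

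The word floating does not let later quitters in. Under Other smoking-related measures, "Participants who were not abstinent at 3 months but have biochemically confirmed abstinence at 9 months will be contacted at 15 months", and their 6 months of abstinence are counted from 9 to 15 months as a separate outcome.

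The smoking measure from which a 3-month change would most naturally be formed is listed under Analysis of secondary outcomes: "Number of cigarettes used on an average day over the past week (including equivalent cigars, tobacco) at 3, 9 and 15* months post-baseline". The mediation section does not say whether change means percent change, absolute change or a category.

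**The concern.** A mediator should be able to vary without fixing the outcome. Here 3-month smoking is both the proposed mediator and the first condition of the outcome. A participant who has cut down by 90% at month 3 and one who has not cut down at all both have outcome 0 by definition. A participant who tapered gradually to zero and one who stopped abruptly have the same mediator value, a 100% reduction. The analysis therefore has no information on whether partial or gradual reduction helps people quit.

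That question is central to the trial. The stated aim (Aims & objectives) is that supported reduction should lead to more quit attempts and then to prolonged abstinence. The mediation analysis runs only when the trial is positive, which is when a claim about mechanism would draw attention. A large share mediated by reduction in smoking could then be reported as support for the reduction theory, although abrupt quitting would produce the same figure.

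**Working it through.** **Inputs from the document.** Control rate 5%, intervention rate 11%, two-sided Fisher exact test, 90% power, N = 900, 1:1 (Determination of sample size).

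**The plan's own figures.** Exact enumeration of the Fisher test gives power 0.9003 at 450 per arm and 0.8995 at 449 per arm, so 900 is reproduced. The odds ratio is (0.11/0.89)/(0.05/0.95) = 2.348, which matches 2.35. Nothing below affects these.

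**Structure of the outcome.** Let q = P(verified abstinent at 3 months) and m = P(stays abstinent to 9 months, given abstinent at 3 months). Then P(outcome) = q × m in each arm, and P(outcome | smoking at 3 months) = 0 in each arm.

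**Splitting the effect through 3-month abstinence.**

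- Total = q1·m1 − q0·m0
- Through month 3 = (q1 − q0)·m, with m taken from either arm
- Remainder = q·(m1 − m0), with q taken from the other arm

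The document gives neither q nor m. The values below are assumptions, chosen so that each row gives 5% versus 11%, a total of 0.06.

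| Scenario | q control, intervention | m control, intervention | Through month 3 | Share |
|---|---|---|---|---|
| (a) effect only on being abstinent at month 3 | 10%, 22% | 50%, 50% | 0.12 × 0.50 = 0.060 | 100% |
| (b) effect on both parts | 12.5%, 20% | 40%, 55% | 0.075 × 0.55 = 0.041, or 0.075 × 0.40 = 0.030 | 69% or 50% |
| (c) effect only on later relapse | 12.5%, 12.5% | 40%, 88% | 0 | 0% |

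The share thus tells the reader when the effect arose. No row involves partial reduction at all, since q and m fix the result whatever the 3-month smokers did.

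**How many participants carry no information on reduction.** In (a), 450 × 0.90 + 450 × 0.78 = 405 + 351 = 756 of 900 (84%) would be smoking at month 3. In (c), it is 900 × 0.875 = 787.5 (87.5%). All have outcome 0, so the outcome does not vary with the size of their reduction. Among the remaining abstainers the percent reduction does not vary, because it is 100% for all. The mediator-to-outcome association is then only the contrast between abstainers and smokers.

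**Model behaviour.** One data set of 900 was simulated for each of (a) and (c), with 3-month abstainers given zero cigarettes and everyone else at least one. In both, every success had a 100% reduction and none came from a 3-month smoker. A logistic regression of outcome on arm and mediator gave:

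| Coding of the mediator | Converged? | Mediator coefficient (standardised) |
|---|---|---|
| Percent change | No | SE 826 and 843 after 20 iterations |
| 3-month abstinence indicator | No | SE 581 and 504 after 20 iterations |
| Absolute change plus baseline cigarettes | No | SE 1087 and 929 after 20 iterations |
| Absolute change alone | Yes | 1.22 (SE 0.12) and 1.53 (SE 0.13) |

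The first three are quasi-separated. Absolute change alone can be fitted, but it carries the same built-in link. Among abstainers, absolute change is simply baseline consumption.

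**The case against.** A reader might infer something stronger: that the smoking pathway is true by definition, so the analysis would report close to 100% mediation whatever the mechanism. The document does not support that. An indirect effect needs two links, and only the second is built in. Whether allocation changes 3-month smoking is an empirical question. Abstinence at 3 months is necessary but not sufficient, because participants can relapse before 9 months. Scenario (c) gives a share of zero, and a share of 100% appears only if maintenance is assumed equal in both arms.

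Four further points can be made for the plan.

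- **Measurement.** Cigarettes are averaged over the past week, while a quitter is someone who has not smoked since the quit date. A person who stopped a few days before the questionnaire could report some cigarettes and still meet the outcome. This stands: it makes the link largely rather than perfectly built in, and it could break exact separation. The document does not say how many people this would be.
- **Coding.** The article names no metric or model for change, so quasi-separation is a risk under several codings, not a stated feature of the plan. This stands.
- **Status.** The analysis is exploratory and conditional, and the process evaluation also examines progression to cessation by other means. This stands and limits the weight of the point.
- **Left to the SAP.** This does not stand. The article itself fixes the pairing of mediator and outcome.

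**Conclusion.** The point holds in a limited form. Change in smoking to 3 months overlaps with the first component of the primary outcome, so a finding of mediation through it separates effect present by month 3 from effect arising afterwards and does nothing more. It cannot show that reduction led to quitting. Its size is not predictable from the document: 0% to 100% over assumed values of q and m that all give 5% versus 11%. The conclusion rests on the written outcome definition and on 3-month smoking being recorded consistently with verified abstinence, apart from recent quitters.

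Physical activity as a mediator does not share this fault, since it is not part of the outcome definition. It is, however, measured at the same visit point as the first abstinence check, so its order in time is not established. The primary analysis, sample size and secondary comparisons are untouched. The change is worth making because it is cheap and prevents a misleading claim about mechanism.

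**What to change.** In the Mediational analysis section, and in the matching SAP text:

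1. Remove change in smoking to 3 months as a mediator of the primary outcome. Keep physical activity for that outcome, together with the process measures that the process evaluation section names as mediators of smoking outcomes.
2. Test the reduction pathway on CO-verified point prevalence abstinence at 9 months, which is already a listed secondary outcome and does not require abstinence at 3 months. Those who meet the primary outcome also count as abstinent here, so changing the outcome alone does not remove the overlap. Estimate the reduction term among people still smoking at 3 months, or include 3-month abstinence as a separate indicator so that those people inform it.
3. State how change in smoking is coded.
4. State the limits: the analysis conditions on a status reached after randomisation, is a non-randomised comparison, and may rest on few people who quit after month 3. Report it as exploratory.

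If the present analysis is kept for any reason, describe the share as the part of the effect present by month 3, not as mediation by reduction.

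The cost is a wording change with no new data. The article says the SAP was still to be approved before database lock.

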#### Randomisation

Participants were individually randomised to either the intervention or control group (1:1 ratio) following completion of baseline assessments, to ensure concealment was preserved. Randomisation was achieved by means of a 24-hour web-based system created by the UKCRC-registered Peninsula Clinical Trials Unit (CTU) in conjunction with a statistician independent from the trial team, and used random permuted blocks, with stratification for recruitment site and a dichotomised low/high score derived from the Heaviness of Smoking Index (HSI).^29^ The HSI score is calculated from summing responses to two questions:

When the first cigarette is smoked after waking, scored as >60 min (score 0); 31–60 min (1); 6–30 min (2) and within 5 min (3).How many cigarettes are smoked in a typical day, scored as ≤10 cigarettes (0); 11–20 cigarettes (1); 21–30 cigarettes (2); >30 cigarettes (3).

Total HSI scores of 0–4 were categorised as low, and 5–6 were considered high for the purposes of stratification.

Following randomisation, all participants were sent a letter from the coordinating CTU confirming which trial arm they had been assigned to, and a guidance sheet on usual support locally for smoking reduction and cessation. The participant’s GP was also sent a letter notifying them that one of their patients is participating in the study.

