#### PA measures

The 7-day recall measure of PA^43^ is used to assess self-reported weekly minutes of moderate and vigorous PA. An objective measure of total weekly minutes of moderate and vigorous PA (MVPA) was collected with a wrist-worn waterproof GENEActiv accelerometer^44^ around the 3-month follow-up time point. Participants were asked to wear the accelerometer on the wrist of the non-dominant hand constantly for 1 week and then return to the CTU. This accelerometer shows the wearer no information about their PA levels and does not have obvious motivational value.

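### The physical activity mediator is a change score, and baseline activity is not among the covariates named; if the 3-month level is what drives abstinence, a real activity pathway could be missed

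*Protocol article*

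**What the plan says.** In the protocol article, the Mediational analysis section defines the mediators as changes and names the adjustment set: the effect on the primary outcome is to be examined as "mediated by changes in smoking and/or physical activity between baseline and 3-month follow-up, adjusted for the stratification variables (site and HSI"). The analysis is exploratory and conditional: "If there is evidence that the intervention is effective, an exploratory mediational analysis will be undertaken".

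The section Analysis of secondary outcomes starts from the same two covariates, site and HSI, but adds "as well as baseline values of the outcome as appropriate". The mediation section has no such clause.

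Three other places matter:

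- Activity at both time points comes from "The 7-day recall measure of PA" (PA measures), which Table 1 schedules at baseline and at 3 months. The accelerometer is used only at 3 months, in a subsample, so it cannot supply a change.
- HSI, which is adjusted for, includes the item "How many cigarettes are smoked in a typical day" (Randomisation). It therefore carries baseline smoking in bands, but not baseline activity.
- The outcome in the mediation model is "Biochemically verified 6-month floating prolonged abstinence between 3 and 9 months" (Primary outcome measure), so every success must already be abstinent at 3 months.

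**The concern.** Write M0 and M3 for activity at baseline and at 3 months. A model containing M3 - M0 but not M0 imposes coefficients on M0 and M3 that are equal in size and opposite in sign. If the likelihood of sustained abstinence depends on how active the person is at 3 months, the M0 part of the score is noise as far as the outcome is concerned, and the slope shrinks. HSI offers no protection, because nothing in it measures activity.

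Physical activity as a route to abstinence is what distinguishes this trial. Mechanisms of action are a listed aim, and the process evaluation names mediation of smoking outcomes by activity as a target. If the intervention works, readers will look to this analysis to see whether activity contributed. A null answer produced by the way the mediator was entered would mislead them.

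**Working it through.** **The plan's own figure.** The article gives no figure for the mediation analysis. Its sample size reproduces: "the sample size calculation was based on a two-sided Fisher exact test", and exact enumeration for 5% versus 11% gives power 0.9003 at 900 in total and 0.8995 at 898. The odds ratio is (0.11/0.89)/(0.05/0.95) = 2.348, stated as 2.35. N = 900 is used below.

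**Assumed inputs.** The documents give no SD of activity at either time, no baseline-to-3-month correlation (rho), and no slope of abstinence on activity. The assumptions are rho from 0.3 to 0.7, an SD ratio s = SD3/SD0 from 0.85 to 1.5, and a log odds ratio b per baseline SD of 3-month activity.

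**Step 1: the mediator-outcome slope if the level matters.** With SD0 = 1, regressing on D = M3 - M0 without M0 multiplies b by

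Cov(M3, D)/Var(D) = (s² - rho·s)/(1 + s² - 2·rho·s).

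At s = 1 this is (1 - rho)/(2(1 - rho)) = 0.50 for any rho. Otherwise:

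| s | rho = 0.3 | rho = 0.5 | rho = 0.7 |
|---|---|---|---|
| 0.85 | 0.39 | 0.34 | 0.24 |
| 1.00 | 0.50 | 0.50 | 0.50 |
| 1.25 | 0.66 | 0.71 | 0.85 |
| 1.50 | 0.77 | 0.86 | 1.04 |

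**Step 2: check in the logistic model.** Simulation with 400,000 participants, b = 0.50, s = 1, site and HSI in the model, HSI unrelated to baseline activity:

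- The level drives the outcome: change without baseline gives 0.24 to 0.25; with baseline added, 0.50.
- Change drives the outcome: about 0.50 with or without baseline.

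**Step 3: why change or level is then immaterial.** Since b3·M3 + b0·M0 = b3·(M3 - M0) + (b0 + b3)·M0, the mediator coefficient is b3 in either coding once M0 is in the model.

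**Step 4: the arm-to-mediator path at s = 1.** In units of the common variance, the residual variance is 2(1 - rho) for the change and 1 - rho² for the 3-month value given baseline. The ratio is 2/(1 + rho): 1.54, 1.33 and 1.18 at rho = 0.3, 0.5 and 0.7.

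**Step 5: what this does to detection.** Power for the mediator-outcome path at N = 900, rho = 0.5, s = 1, complete data, when the level drives the outcome (600 replicates):

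| b | Change, site, HSI | Baseline activity added |
|---|---|---|
| 0.3 | 21% | 55% |
| 0.4 | 35% | 76% |
| 0.5 | 51% | 93% |

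**Step 6: where the argument stops.**

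- *Smoking mediator.* HSI already carries banded baseline cigarettes. With an assumed correlation of 0.6 between HSI and baseline, the change-only slope is 0.31 to 0.32 against 0.50, a factor of about 0.62 rather than 0.50. That calculation treats the mediator as freely varying, which 3-month smoking is not. Every primary-outcome success must be abstinent at 3 months, so change plus baseline fixes 3-month cigarettes, and anyone above zero is a failure by definition. This is quasi-complete separation, and a trial logistic fit of that form at N = 900 did not converge.
- *Process-measure models.* Their outcomes are themselves changes in smoking and activity. If one relation holds at both times, change on change is a first-difference estimator. A simulation with true slope 0.40 returned 0.40 at rho = 0.3, 0.5 and 0.7.

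**The case against.** The strongest reply is that one sentence of a journal article is not a model. The text does not say that baseline activity is excluded; it gives no mediator or outcome equation, and a detailed analysis plan exists that is not shown. A reader might infer that baseline adjustment has been ruled out, but the article does not support that. What it supports is narrower: it lists the covariates, baseline activity is not among them, and the same article writes baseline values out where it intends them.

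Second, the trial's rationale is framed as increasing activity. If change is the active quantity, the stated form is unbiased. This stands, and it makes the attenuation conditional. It does not favour the stated form, because the baseline-adjusted model is right in both cases.

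Third, a reader might infer that every mediator path is roughly halved. The documents do not support that either. Halving needs equal SDs, which are not given; the loss differs for smoking; and the process-measure models have a different structure.

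Fourth, a baseline-adjusted comparison of 3-month activity between arms is already planned as a secondary outcome. That largely covers the arm-to-mediator question on its own, but not the mediator-outcome path.

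**Conclusion.** The point holds for physical activity in the mediation analysis of the primary outcome. If the 3-month level drives abstinence, the slope is halved at equal SDs, falls to 0.24-0.39 of its value at an SD ratio of 0.85, and to 0.66-0.85 at 1.25. By a ratio of 1.5 there may be little or no attenuation (0.77-1.04). If change drives abstinence there is none. The loss of precision in the arm-to-mediator path applies under either mechanism at equal SDs. All sizes rest on assumed correlations, SD ratios and slopes.

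The importance is limited. The analysis is exploratory and runs only if the intervention appears effective, and neither the primary result nor the sample size is touched. What is at risk is the reading of a null activity pathway.

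**What to change.** State in the analysis plan that, in the mediation analysis of the primary outcome, baseline self-reported MVPA is a covariate, alongside site and HSI, in both the mediator model and the outcome model. The activity mediator may stay as change or become the 3-month value; its coefficient is then the same.

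Do not apply this rule to the smoking mediator, because of the separation described above, and do not justify it for the process-measure models by the same attenuation argument.

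The cost is one line of text and one extra covariate in an exploratory model. Both measurements are already scheduled. At the design rates there would be about 450 × 0.05 + 450 × 0.11 = 72 abstinent participants, so one more term is affordable.
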